**6. STUDY DESIGN**

Stage 2

Blinded, placebo/sham-controlled trial consisting of 40 participants. Group 1 (20 participants) will be

participants with Parkinson’s disease receiving treatment and Group 2 (20 participants) will be a placebo/sham-control group receiving no treatment. All groups will begin intervention in

August 2021. Treatment will consist of PBMt to the head and nose (either active or

placebo treatment), 3 times per week for 12 weeks. Outcome measures to be collected by Specialist

Examiners and the Physiotherapists.

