**8. STUDY POPULATION**

Two groups of participants will be recruited: 20 participants with PD receiving active intervention (Group 1) and 20 participants with PD receiving sham/placebo intervention (Group 2)

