**8c. Sample size**

- Group 1 - 20 participants
- Group 2 - 20 participants

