**13. DATA ANALYSIS**

**13a. Outcome measurements**

Baseline data for all outcome measures collected before the beginning of treatment will form the reference point for analyses.

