**13b. Statistical analysis**

As a series of N=1 studies, it is anticipated that only basic statistical analysis will be performed. For each outcome measure, descriptive data (mean, standard deviation) will be calculated. From this data, “minimally important difference” (MID) scores will be computed based on ½ SD of each measure. This is a common MID measure (Norman et al, 2003) based on the distribution of the participant scores at baseline and provides a sensitive indicator of significant change over time for N=1 case studies. As such, it does not suffer from a lack of statistical power that would be evident with more traditional ANOVA approaches with small sample sizes. The number of participants showing improvement (i.e., difference between two time points > MID) can be compared between time points with chi-square analyses.

Participants showing improvement in the Sydney arm of the multi-centre Parkinson’s trial will be compared to the Brisbane and Adelaide arms (chi-square analysis) in order to establish optimum PBM areas of treatment and doses regimens.

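### Section 13b states no active-versus-sham comparison; its only tests are between time points and across trials, so the sham group is not used as a control

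*Protocol*

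**What the plan says.** Design: Protocol Section 6 sets out a "Blinded, placebo/sham-controlled trial consisting of 40 participants". Section 8 gives the groups as "20 participants with PD receiving active intervention (Group 1) and 20 participants with PD receiving sham/placebo intervention (Group 2"), and Section 8c repeats 20 per group. Section 3 makes efficacy against Parkinson's symptoms the main aim.

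Analysis: Section 13a says "Baseline data for all outcome measures collected before the beginning of treatment will form the reference point for analyses". Section 13b opens with "As a series of N=1 studies, it is anticipated that only basic statistical analysis will be performed". It then says that minimally important difference (MID) "scores will be computed based on ½ SD of each measure", taken from the baseline distribution. Two tests follow:

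- within the trial, "The number of participants showing improvement (i.e., difference between two time points > MID) can be compared between time points with chi-square analyses";
- across trials, a chi-square comparison of Sydney improvers with the Brisbane and Adelaide arms.

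No section of the protocol states a comparison of Group 1 with Group 2. Section 13b does not say which chi-square test is meant, whether improvers are counted per group or over all 40 participants, or whether sham participants are left out of the cross-trial count.

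**The concern.** A sham arm separates the effect of the device from everything else that moves scores over 12 weeks: expectation, learning the tests, regression to the mean and plain test-retest noise. Only a comparison between the groups does this. A contrast between time points in the same people contains all of these influences, and a contrast with other trials adds differences in population, setting and treatment.

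This is more than silence that an analysis plan would fill. Section 13b states an analysis and argues for it, on the ground that the MID approach escapes the low power of ANOVA in small samples. The analysis it states does not match the design in Sections 6 and 8. A plan written faithfully to 13b would inherit the wrong contrast, and an active arm that improved no more than sham could still be reported as a positive result.

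**Working it through.** **Design against analysis**

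| Element | Design (Sections 3, 6, 8) | Analysis (13a, 13b) |
|---|---|---|
| Unit of inference | two groups of 20 | single cases |
| Reference | sham group | each participant's baseline |
| Within-trial test | none named | improvers, time point v time point |
| Between-group test | implied by sham control | Sydney v other trials only |

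The active-versus-sham cell is empty. The protocol gives no numerical result on this point to reproduce: Section 8c states 20 per group without alpha, power, effect or SD.

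**Inputs for the illustration.** From the protocol: 20 per group, threshold of half a baseline SD, assessments at weeks 0, 4 and 12. Assumed: normal scores with SD 1, test-retest correlation r of 0.7 to 0.9, two-sided alpha 0.05.

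**Step 1: improvers by noise alone.** The SD of a change score is √(2(1−r)), so P(change > 0.5 SD) = 1 − Φ(0.5/√(2(1−r))).

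- r = 0.7: 0.5/0.775 = 0.645, giving 0.259
- r = 0.8: 0.5/0.632 = 0.791, giving 0.215
- r = 0.9: 0.5/0.447 = 1.118, giving 0.132

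So 26% to 13% count as improved with no change at all.

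**Step 2: no device effect, same shift in both arms.** Scores are √r·T + √(1−r)·E, with T fixed for a person and E new at each visit. Both arms have no shift at week 4 and a shift of 0.3 or 0.6 SD at week 12. Improvers are counted against baseline. For counts a and b out of 20, the Pearson statistic is ((a−b)/20)² / (p(1−p)·2/20), with p = (a+b)/40. Rejection rates over 40,000 runs, with the threshold fixed at 0.5 SD:

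| Shift | r | Time-point Pearson, active arm | Time-point McNemar, active arm | Active v sham, week 12 |
|---|---|---|---|---|
| 0.3 | 0.7 | 11% | 18% | 5% |
| 0.3 | 0.8 | 16% | 24% | 5% |
| 0.3 | 0.9 | 29% | 38% | 5% |
| 0.6 | 0.7 | 46% | 58% | 5% |
| 0.6 | 0.8 | 65% | 75% | 5% |
| 0.6 | 0.9 | 92% | 95% | 5% |

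A separate 5,000-run check, with the SD estimated within each arm, gave 11% to 92% for Pearson and 19% to 95% for McNemar. Active versus sham then rose to about 6% to 10%, because the two arms were held to different thresholds. A common threshold avoids that excess.

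**Step 3: no shift at all.** Pearson applied to the paired week-4 and week-12 counts rejects in about 2% of runs, and McNemar in about 4% to 5%. Ignoring the pairing therefore makes the test conservative. It does not create false positives.

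**The case against.** The strongest reply is that 13b is permissive (it speaks of what is anticipated and what can be done), that both groups are measured on the same schedule, and that an analysis plan not shown here could add the group comparison. The data would indeed support it, so the trial as designed can still address its efficacy aim. What fails is the stated analysis.

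A second reply is that 20 per group is weak for a group comparison. That is true. At 80% power the detectable difference is (1.960 + 0.842)·√(2/20) ≈ 0.89 SD, and power for 0.5 SD is about 35%. But a within-person test does not recover that power, because it answers a different question. Section 15 also wants this study to inform the sizing of a larger placebo-controlled trial, and that requires an estimated group difference with its uncertainty.

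Three stronger readings are tempting, and the protocol does not support them:

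- **That the chi-square is an independent-samples test and so invalid.** Pearson is the natural reading, but the type is not given and McNemar is also a chi-square test. If Pearson is meant, the cost is lost power.
- **That the sham data are discarded.** The SDs, MIDs and improver counts are not restricted to Group 1, so sham participants may enter all of them. They are unused as a control.
- **That improvers would be tested against a baseline count of zero.** Section 13a makes baseline the reference for change, and 13b defines improvement as a difference between two time points. No improver count at baseline is defined.

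**Conclusion.** The point stands as wrong as written, and it must be fixed. Section 13b names no active-versus-sham comparison in a 20 v 20 sham-controlled trial with an efficacy aim, and neither of its two tests can stand in for one. The main harm is the uncontrolled contrast over time. The unspecified chi-square is secondary, and a paired test alone leaves the main problem in place, as the McNemar column shows.

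The absence of the comparison is read directly from the text and needs no assumption. The percentages do rest on assumptions: normal scores, correlations of 0.7 to 0.9, a shared shift of 0.3 to 0.6 SD arising between weeks 4 and 12, and a test run in the active arm alone. They show how large the error could be and do not predict it for any one measure.

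**What to change.** In Section 13b:

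1. Delete the opening clause that treats the trial as a series of single-case studies.
2. State the main analysis as Group 1 versus Group 2 at week 12: a baseline-adjusted difference with 95% CI (ANCOVA) for the quality-of-life score and the other continuous scored measures. Week 12 suits this because Section 14 offers sham participants active treatment after it. ANCOVA need not be extended to microbiome composition or the carer diary, which require their own methods.
3. Keep improver proportions as supportive, compared between groups (for example by Fisher's exact test), with one MID per measure from the baseline SD of both groups together.
4. Label any within-group contrast of time points as secondary and use a paired method such as McNemar.
5. State that the comparison with Brisbane and Adelaide does not replace the sham comparison, and which Sydney participants enter it.

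Baseline and week-12 measures are already scheduled in both groups, so no new data are needed and the change is one of wording, best made before unblinding. One item must be settled with it: the primary outcome in Section 11 is improved quality of life with no instrument named, while the PDQ-39 is listed as secondary. The score for the main analysis has to be named.

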The applicability of PBMt, the positive animal study responses and the lack of side effects suggest that PBMt could provide a viable adjunct to current treatments for PD. No study has yet explored this method of treatment in humans. We propose to trial the PBMt in a series of case studies to best identify the type of application, the site of application and dose rate that may produce positive changes in clinical signs and functional capacity of people with PD. Given that abscopal effects (where treatment in one part of the body can influence remote sites) are known for PBMt, our research seeks to understand whether site of PBMt application influences clinical signs and functional capacity of people with PD, in the same way that dosing may do. Hence, a Brisbane arm of our parallel studies (with separate HREC application) will evaluate the effect of PBMt to the head of eligible participants with PD whilst the Sydney arm will evaluate the effect of PBMt on the abdomen and spine. The abdomen is a critical site due to recent evidence proposing a link between the gut and brain associated with PD (Pellegrini et al, 2015). The spine as part of the central nervous system is a key site of application due to its links with the brain. This HREC application is specific to the Sydney arm of our parallel studies.

Investigators in our team have already established the efficacy and safety of PBMt in animals (rodents and primates) using an invasive technique (Darlot et al, 2016). Based on recent studies of transcranial PBMt in humans with traumatic brain injury, stroke and dementia, we know that it is not necessary to apply PBMt utilizing a surgical method. We intend to use a non-invasive remote site approach in order to measure any abscopal effect.

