The Sydney proof-of-concept trial follows on from proof-of-concept trials which have been completed in Brisbane and Adelaide. The Brisbane trial was a randomised placebo trial using transcranial photobiomodulation and showed significant differences between the treated and placebo group. The Adelaide trial was a waiting-room design with transcranial, intranasal, cervical spine and abdominal photobiomodulation; results are still being analysed but look very encouraging, including potentially positive changes in the microbiome. The Sydney trial will be a case-matched trial and use abdominal and cervical spine photobiomodulation only. The Sydney trial will be conducted over a 12-week treatment period and will assess a number of outcome measures, including motor abilities, cognitive function, microbiome changes, cytokine levels and potential Parkinson’s disease marker changes, as well as self and carer assessments of wellness. The trial is to be conducted in two stages: an initial cohort will be assessed in September, to begin treatment in October. A further cohort will begin treatment in August 2021. The funding for the Sydney trial has been provided by the San Foundation and from private donors. Additional funding ($27,000) has been obtained to conduct the second stage of the trial. The results from all three trials will be used to argue for a large-scale, randomised, double-blinded trial.

The idea for this study emerged after a previous study evaluating the application of photobiomodulation in participants with PD was completed (approved by Griffith University HREC). Ethics approval for this study is being sought through the AHCL HREC. This study will be a simplified blinded placebo/sham-controlled trial with the following sites:

- Northshore Musculoskeletal and Laser Physiotherapy Clinic, [name].
- Photobiomodulation Clinic, Specialist and GP Centre, San Hospital, [name]
- [name], San Hospital, [name]

The sponsor and the supplier of devices for this study will be SYMBYX Biome Pty Ltd, [name]

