**12. STUDY PROCEDURES**

**11a. Study procedure**

The PBMt intervention will consist of 3 treatment sessions per week for 12 weeks (Groups 1). Participants in the active treatment group will receive transcranial light treatment with a PDNeuro LED helmet device (parameters given in Appendix 1). The treatment areas are 20 points (

154.5 joules total energy). The treatment time is 24 minutes. Participants in the placebo/sham group (Group 2) will receive the same apparent treatment as Group 1, except that they will be “treated” with sham transcranial LED devices that delivers no light.

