**15. OUTCOMES AND SIGNIFICANCE**

The results of this study (will inform the researchers as to which dose and site of application, if any, influences outcome measures for people with Parkinson’s Disease. This information will provide the foundation dose methodology for a larger placebo-controlled trial for this patient population as well as information required to adequately power a larger trial.

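### A chi-square test of improver counts against the separate Brisbane and Adelaide trials cannot establish the best treatment site or dose, because both are confounded with trial

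*Protocol*

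**What the plan says.** Section 13b (Statistical analysis) sets a minimally important difference (MID) for each measure at half the SD of participants' baseline scores. A participant whose change between two time points exceeds it counts as improved. The section plans a chi-square comparison of improvers between time points, and then states that improvers in the Sydney arm "will be compared to the Brisbane and Adelaide arms (chi-square analysis) in order to establish optimum PBM areas of treatment and doses regimens".

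Section 2 (Background) describes the comparators: "The Brisbane trial was a randomised placebo trial using transcranial photobiomodulation", and "The Adelaide trial was a waiting-room design with transcranial, intranasal, cervical spine and abdominal photobiomodulation". On Sydney it says that "the Sydney arm will evaluate the effect of PBMt on the abdomen and spine" and, later, "The Sydney trial will be a case-matched trial and use abdominal and cervical spine photobiomodulation only".

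Section 6 (Study design), under the label Stage 2, is different: "Treatment will consist of PBMt to the head and nose", active or sham, 20 participants per group. Section 11a agrees: the active group "will receive transcranial light treatment with a PDNeuro LED helmet device".

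Section 15 (Outcomes and significance) says the results "will inform the researchers as to which dose and site of application, if any, influences outcome measures", and that they will supply the dose methodology for a larger placebo-controlled trial.

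**The concern.** The protocol names the test, the data, the comparators and the conclusion to be drawn. A statistical analysis plan could add detail, but no detail would let this test support that conclusion. Comparing three separately run studies by raw counts attributes every difference between them to site and dose. Expectancy, type of control, period and patient mix would all be read as effects of where and how much light was given.

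The consequence falls on the next trial. Section 15 passes the site and dose conclusion forward as the basis for its regimen. This stage's main protocol has one device regimen and a sham. It can estimate that regimen against sham, but it holds no comparison of sites or doses.

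**Working it through.** The protocol gives no alpha, power, effect size or sample size for the cross-trial test, so there is no stated figure to reproduce. The check sets the three trials side by side and then illustrates the size of the bias on assumed values.

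**1. What changes with trial (Protocol Sections 2, 6, 11a, Appendix 1)**

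| | Brisbane | Adelaide | Sydney, Stage 2 |
|---|---|---|---|
| Site | transcranial | transcranial, intranasal, cervical spine and abdomen together | head and nose |
| Control | randomised placebo | waiting-room | sham |
| Status | completed | completed | from August 2021 |
| Group sizes | not given | not given | 20 and 20 |

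All three include transcranial light. Adelaide's four sites were treated together, so they cannot be separated even within that trial. No pair of columns differs only in site or only in dose. If the contingency protocol in Appendix 8 is used, Sydney sessions go from 3 to 6 per week, and regimen then varies within Sydney as well.

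**2. What raw improver counts contain**

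Assume normally distributed scores with equal SD at both visits and test-retest correlation r. In baseline SD units, change has SD √(2(1−r)). If the mean shift is m, then

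P(improved) = 1 − Φ((0.5 − m) / √(2(1−r))).

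With r = 0.7, the SD of change is √0.6 = 0.775.

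- m = 0: 1 − Φ(0.5/0.775) = 1 − Φ(0.645) = 26%.
- m = 0.3, from expectancy alone: 1 − Φ(0.2/0.775) = 1 − Φ(0.258) = 40%.

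Neither r nor m is in the protocol. Over a range of r:

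| r | m = 0 | m = 0.3 |
|---|---|---|
| 0.5 | 31% | 42% |
| 0.7 | 26% | 40% |
| 0.9 | 13% | 33% |

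So 13% to 31% count as improved with no effect at all. A 0.3 SD difference in expectancy adds 11 to 20 percentage points with no site or dose effect. At r = 0.7, a smaller shift of 0.1 SD gives 30%, and 0.2 SD gives 35%.

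**3. The threshold**

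The MID comes from the participants' own baseline SD. With n = 20, the 95% sampling range of an SD estimate is √(χ²/19) at the 2.5% and 97.5% points, or 0.68 to 1.31 times the true SD. Two samples from one population can therefore have different thresholds. Section 13b fixes no common value across trials.

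The effect on the counts depends on the assumptions. Take a mean change of 2 points and baseline SDs of 8 and 10. With r = 0.7, the SD of change is 6.20 and 7.75, and the improver shares are 1 − Φ(2/6.20) = 37% and 1 − Φ(3/7.75) = 35%. With the SD of change held at 5 in both, they are 1 − Φ(2/5) = 34% and 1 − Φ(3/5) = 27%. This is a secondary weakness.

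**4. How often the bias in step 2 would reach significance**

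Assume 20 per trial, two-sided 5%, 26% v 40% (0.259 v 0.398). The pooled proportion is 0.3285, the null SE √(0.3285 × 0.6715 × 2/20) = 0.1485, and the alternative SE √((0.259 × 0.741 + 0.398 × 0.602)/20) = 0.1469. Power = Φ((0.139 − 1.96 × 0.1485)/0.1469) = Φ(−1.04), about 15%. The test has little power for real differences either: 25% for 30% v 50%.

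**The case against.** The other side has several good points, and they limit what can be said.

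- A reader might infer that the head versus abdomen contrast with Brisbane no longer exists. The documents do not show that. Section 2 describes two Sydney stages, and the abdomen and spine text may describe the first cohort. If that cohort is included, a non-randomised contrast remains. What stands is that Stage 2 adds no abdomen or spine data, and that Section 13b does not say which cohort or group is compared.
- A reader might infer that the three trials used different MIDs. The protocol states the half-SD rule for Sydney only and is silent on the others, and a statistical analysis plan could fix a common value.
- A reader might infer that all three designs are mismatched. Brisbane and Stage 2 both have a placebo or sham control, so the clear mismatch is Adelaide's waiting-room design. Stage 2 does not copy Brisbane either, because it adds a nasal LED.
- A reader might expect a false optimum to be declared significant. On the assumed figures that happens only about 15% of the time. Section 13b names no significance level for declaring an optimum, however, and a non-significant result from so weak a test would not show that sites are equivalent.
- Section 15 is hedged, and Section 2 says the three trials will be used to argue for a large randomised trial. That lowers the stakes, but Section 15 still passes a dose methodology forward.

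None of this rescues the stated inference. Site and dose remain confounded with trial.

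**Conclusion.** The concern holds. An unadjusted chi-square on improver counts across three separately run studies cannot establish an optimum site or dose. This follows from the designs as described and does not depend on the illustrative numbers. On the assumptions shown (normal change, r = 0.7, no site effect), a 0.3 SD expectancy difference moves improvers from 26% to 40%. Across r from 0.5 to 0.9 the move is 11 to 20 percentage points. The actual bias cannot be computed, because the protocol gives neither the other trials' group sizes nor their control responses.

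The point should be fixed but is not critical. The comparison of active with sham within this trial is untouched, and the damage is confined to the site and dose claim and to the planning that would rest on it.

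**What to change.** 1. In Section 13b, delete the stated purpose of establishing optimum treatment areas and dose regimens, and remove the cross-trial chi-square as an inferential test.
2. Name active versus sham within this trial as the main comparison.
3. If a cross-trial comparison is kept, label it descriptive, non-randomised and hypothesis-generating. State which Sydney cohort and group it uses, and apply one pre-set MID per measure in all trials. Where the other trials' control data are available, show each trial's active minus control difference with a 95% CI in place of raw counts.
4. Reword Section 15 to say that this stage estimates one device regimen against sham and does not show which dose or site works.
5. Reconcile the statements on the treated site in Section 2 with those in Sections 6 and 11a, saying which cohort each describes.

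Items 1, 2, 4 and 5 are changes of text. Item 3 needs a little extra analysis and depends on Brisbane and Adelaide control-group data, which the protocol does not show to be available. The sponsor gives up a site and dose claim that the data could not support.
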